##### 2. Visual analogue scale (VAS) - 'First-step' pain

Severity of pain at the heel when getting out of bed in the morning (also referred to as 'first-step' pain), over the past week, will be assessed using a 100 mm visual analogue scale (VAS). The left side of the scale (0 mm) will be labeled 'no pain' and the right side of the scale (100 mm) will be labelled 'worst pain imaginable'. The VAS is widely used and is valid [38] and reliable [39].

#### Secondary outcome measures

##### 1. Foot Health Status Questionnaire (FHSQ) - foot function and general foot health

Foot function and general foot health will be assessed using the Foot Health Status Questionnaire [36].

##### 2. Short form-36 (SF-36) - health-related quality of life

Health-related quality of life will be assessed using the Short Form-36 version 2 (SF-36). The SF-36 is a 36 item health-related quality of life survey that measures the impact of functional health and well being from the patient's perspective. The SF-36 is widely used and has been extensively validated (concurrent, content, construct, criterion and predictive validity) and has good test-retest reliability [40-42].

##### 3. Depression, Anxiety and Stress Scale short version (DASS-21)

The severity of symptoms of depression, anxiety and stress will be determined using the short version of the Depression, Anxiety and Stress Scale (DASS-21) [43]. The DASS-21 contains 21 items in total that assess the severity of each condition. Participants will be asked to use a 4-point severity/frequency Likert scale to rate the extent to which they have experienced each state over the past week.

Scores for depression, anxiety and stress will be calculated by summing scores for relevant items. High scores on the DASS-21 indicate a high level of distress in the participant. The score for each condition is then evaluated as per the severity-rating index (i.e normal to extremely severe). The DASS-21 has been shown to have high internal consistency and temporal stability [43]. The DASS-21 has been previously validated (content, construct, convergent and discriminative validity) [43,44].

#### Other measures

##### 1. Adverse events

A pre-specified checklist of potential adverse events will be administered so that any adverse event experienced since the previous treatment can be recorded. An open-response type format will also be available for participant responses. Participants will be asked to rate the perceived degree of severity (mild, moderate and severe) for each type of adverse event. In addition, the chief investigator will record adverse events that occur during the treatment.

All adverse events will be classified as non-serious (pain at the site of needle insertion; bleeding; feeling faint; drowsiness; nausea; sweating; infection; needle allergy; exacerbation of symptoms) or serious (any adverse event that leads to serious disability; hospital admission; is life threatening or results in death) as defined by Australia's Therapeutic Goods Administration [45]. A detailed description will be made of any adverse event that results in withdrawal of participants from the trial.

##### 2. Use of rescue medication to relieve plantar heel pain

Participants will be required to complete a medications diary to record the type and amount of rescue medication consumed for their plantar heel pain. Rescue medication is defined as medication (e.g. paracetamol) participants can use during the study, if required. The diary will be returned to the Chief Investigator at 6 and 12 weeks. The number of participants that consume rescue medication and the average amount of medication (mean grams of paracetamol/participant/month) [26,33] will be determined.

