### Participants

Participants with plantar heel pain that provide informed consent will be recruited from the local community via:

i) Advertisements in local and greater Melbourne newspapers;

ii) Mail-out advertisements to local medical and allied health practitioners;

iii) Advertisements on relevant internet sites;

iv) Posters displayed in local community centres, sporting clubs, retirement villages, Melbourne universities;

v) Advertisements on Melbourne radio.

People interested in the study will be instructed to contact the Chief Investigator ([name]) via phone or email and will be screened for eligibility. Respondents that are deemed suitable for the study will be invited to attend an initial assessment at the La Trobe University Health Sciences Clinic. To be included in the study, participants must meet the following inclusion criteria:

i) Age greater than 18 years;

ii) Clinical diagnosis of plantar heel pain in accordance with the Clinical Guidelines linked to the International Classification of Function, Disability, and Health from the Orthopaedic Section of the American Physical Therapy Association [8]. The criteria will include:

• Pain in the plantar medial heel region;

• Plantar heel pain that is aggravated by weightbearing activities and worse in the morning and/or upon weightbearing after periods of rest;

• Pain on palpation of the medial calcaneal tubercle.

iii) History of plantar heel pain for greater than one month;

iv) First step pain during the previous week rated at least 20 mm on a 100 mm visual analogue scale;

v) Participants must be willing to attend the La Trobe University Health Sciences Clinic for an initial assessment and then be randomly assigned to receive either the *real *or *sham *intervention. In addition, participants must be willing to receive one treatment per week for a total of six weeks;

vi) A willingness to not receive or implement any form of physical therapy (e.g. foot orthoses, night splints, foot taping, massage therapy and/or footwear modifications) for the duration of the trial;

vii) Be willing to discontinue taking all pain relieving medications (analgesics and non-steroidal anti-inflammatory medications (NSAIDS), except paracetamol up to 4 g/day, taken by mouth or applied topically:

• For at least 14 days prior to the baseline assessment;

• During the study period (6 weeks after the final treatment).

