##### 3. Use of co-interventions to relieve plantar heel pain

Participants will also be asked to complete a diary to outline other treatments they received during the trial period to help relieve their plantar heel pain. Such treatments include oral non-steroidal anti-inflammatories, topical medicaments (such as rubefacients, or topical non-steroidal anti-inflammatories), foot orthoses, night splints, calf stretching, massage therapy, footwear modifications, foot taping, foot injections [33,46]. Participants will also be questioned to determine if they have changed their footwear during the course of the trial. The diary will be returned to the Chief Investigator at 6 and 12 weeks.

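### Both diaries ask only about treatment used for plantar heel pain, so the by-arm picture of analgesic use is incomplete

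*Protocol article*

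**What the plan says.** Restriction (Protocol article, Participants, inclusion criterion vii). Participants must "Be willing to discontinue taking all pain relieving medications", "except paracetamol up to 4 g/day, taken by mouth or applied topically". This holds for 14 days before baseline and then "During the study period (6 weeks after the final treatment"). The text that follows asks paracetamol users to stop at least 24 hours before baseline and before each follow-up assessment. Neither rule mentions the reason for taking the drug.

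Medication diary (Other measures, item 2). The heading is "Use of rescue medication to relieve plantar heel pain". Participants are to "complete a medications diary to record the type and amount of rescue medication consumed for their plantar heel pain". The definition that follows names no indication: "Rescue medication is defined as medication (e.g. paracetamol) participants can use during the study, if required". The planned summary is "The number of participants that consume rescue medication and the average amount of medication (mean grams of paracetamol/participant/month").

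Co-intervention diary (Other measures, item 3). Participants are to "complete a diary to outline other treatments they received during the trial period to help relieve their plantar heel pain". Oral and topical NSAIDs are among the listed examples.

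Adverse events (Other measures, item 1). Pain at the needle site is a listed non-serious event. Participants rate its severity and have an open response. Recording a drug taken for it is not mentioned.

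**The concern.** The trial restricts analgesics by drug and dose but records them by reason. The protocol itself foresees a reason other than heel pain: Table 1, item 4 makes post-needle soreness one of the factors governing the number of insertions, and item 2 allows needling of hip and thigh muscles. Someone who takes paracetamol for a sore buttock and follows the diary instruction literally would not write it down.

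Such a dose acts systemically. It could ease the heel as well, and it could take the place of a dose that would have been recorded as heel-pain rescue. If this happened more often with penetrating needling, the real arm could show less rescue use than its total analgesic intake warrants. A reader weighing a group difference in pain would then see only part of the analgesic use behind it.

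**Working it through.** No figure in the article bears on this point, so the check compares the text and sets out what the recorded comparison leaves out.

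**Step 1: scope of each rule.**

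| Item | Scope as worded |
|---|---|
| Criterion vii restriction | All pain relief except paracetamol up to 4 g/day; any reason |
| 24-hour washout | Paracetamol; any reason |
| Medication diary, heading and instruction | Use for plantar heel pain |
| Medication diary, definition sentence | No reason named |
| Co-intervention diary, heading and instruction | Treatment for plantar heel pain |
| Adverse-event checklist | Needle-site pain and severity; drug not mentioned |

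No other section of the article provides for recording analgesics taken for other reasons.

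**Step 2: what the recorded comparison omits.** Let H, S and O be the mean amounts taken per participant per month for heel pain, post-needle soreness and other reasons. If the diary is completed as instructed, it captures H alone.

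- Recorded contrast = H(real) − H(sham)
- Total contrast = recorded contrast + [S(real) − S(sham)] + [O(real) − O(sham)]

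Use for unrelated reasons should balance in expectation under randomisation. Soreness arises after randomisation and from the treatment itself, so the S term need not balance. If some soreness doses also replace heel-pain doses, H falls as S rises, and the recorded contrast moves away from the total contrast on that account too.

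**Step 3: sign and size of the S term.** The sham needle does not penetrate, which makes S(real) > S(sham) plausible. But it is manipulated with the same technique as the real needle (Sham dry needling), so S(sham) cannot be set to zero. The article gives no value for either. The size is unknown and the sign is a conjecture.

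**Step 4: does the washout close the gap?** First-step pain is rated over the past week, and the washout covers at least the last 24 hours, which leaves up to 7 − 1 = 6 days of the rated week outside it. Treatment is weekly and measures precede any treatment consultation. At weeks 2, 4 and 6 (week 6 being the primary end-point), the days after the previous session can therefore fall inside the rated period. By week 12 soreness from treatment should no longer matter.

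**The case against.** The strongest reply is that nothing here is contradictory. Criterion vii is an eligibility rule about willingness to stop medication, whereas the diary feeds a descriptive measure of heel-pain rescue use. The two have different purposes and need not share a scope, and heel-pain rescue use is a legitimate measure. This stands. A reader might also infer that the diaries fail as a check on adherence to the restriction or the 4 g/day limit, but the article never gives them that task.

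Second, the article condenses a fuller protocol and the diary forms are not shown. The definition sentence names no reason, so some participants may record more widely. This weakens the point without removing it, because the heel-pain limit is stated text, in the heading and the instruction of both diaries.

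Third, the route to an arm difference has many links: soreness bad enough to medicate, a drug taken, a judgement that it was not for the heel, and a different frequency by arm. Several features narrow it. Three of the four muscles assessed first are in the foot, where soreness may be hard to tell from heel pain and may be entered anyway. Needling is eased if poorly tolerated. Exclusion criterion x removes much use for chronic pain or sciatica. Needle-site pain is collected, so an arm difference in soreness would be visible. All of this stands, and it is why the effect on the arms can only be called plausible.

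**Conclusion.** The point holds as a modest gap in recording. As described, analgesics or NSAIDs taken for post-needle soreness or other reasons need not be entered in either diary, so the by-arm account of analgesic use is incomplete and could understate use in the real arm. This rests on two assumptions: that participants follow the diary wording literally, and, for the direction, that soreness leading to medication is commoner with penetrating needling. The first cannot be checked without the forms, and the second is not shown. No size can be derived.

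A reader might infer that the trial loses the ability to judge whether analgesic use differed between groups, or that its pain result is biased. The article supports neither. Heel-pain medication and needle-site pain are still captured in both arms, which leaves a partial picture rather than none. The primary ANCOVA and the sample size are unaffected.

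**What to change.** Word the diary to record every analgesic and anti-inflammatory taken, with date, dose and reason (heel pain, post-needle soreness, other). Report total use and heel-pain use by arm, so that the planned heel-pain measure is kept and the remainder is visible beside it. The article describes recruitment as still to begin, and the change is best made before then because the reason for a past dose is hard to reconstruct. The cost is a slightly longer diary for participants and one more line in the report, with no new visits or staff.

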##### 3. Use of co-interventions to relieve plantar heel pain

Participants will also be asked to complete a diary to outline other treatments they received during the trial period to help relieve their plantar heel pain. Such treatments include oral non-steroidal anti-inflammatories, topical medicaments (such as rubefacients, or topical non-steroidal anti-inflammatories), foot orthoses, night splints, calf stretching, massage therapy, footwear modifications, foot taping, foot injections [33,46]. Participants will also be questioned to determine if they have changed their footwear during the course of the trial. The diary will be returned to the Chief Investigator at 6 and 12 weeks.

##### 4. Seven day Physical Activity Recall (PAR) - level of physical activity in the previous week

The level of activity in the previous week will be evaluated using the 7-day Physical Activity Recall (PAR) questionnaire [34]. The PAR questionnaire estimates the amount of time the participant spent in physical activity, strength and flexibility activities in the seven days prior to completing the questionnaire. The PAR only records physical activity of moderate or greater intensity. The frequency and duration of each activity undertaken is combined with its metabolic equivalent value to calculate the total kilocalories of energy expenditure per day for each participant. The PAR has been shown to have good reliability and validity [34].

##### 5. Credibility/Expectancy Questionnaire (CEQ)

The Credibility/Expectancy Questionnaire (CEQ) [47] will be administered after the first treatment only, which provides a measure of treatment credibility and expectancy. Treatment credibility refers to the patient's beliefs about the logic of the intervention whereas treatment expectancy refers to the patient's beliefs about how much they think they might improve [48]. It has been shown that a patient's expectations and their initial beliefs about the credibility of a given pain treatment affect treatment outcome [48]. Therefore, if differences in patient beliefs are unequal between groups in this trial, the observed outcome might not be attributed to the independent variable (i.e. real dry needling).

The Credibility/Expectancy Questionnaire consists of 6 items, 3 of which are related to the credibility factor and 3 are related to the expectancy factor. For each item, participants will be asked to rate the credibility of the treatment and their expectations on a 9-point Likert scale. High scores on the scale indicate the participant thinks the treatment is credible and either thinks and/or feels the treatment will result in substantial improvement in their symptoms. The Credibility/Expectancy Questionnaire has been shown to have good internal consistency and test-retest reliability [47]. A modified version of the Credibility/Expectancy Questionnaire has been used previously to evaluate the credibility of real dry needling versus sham dry needling for patients with whiplash associated pain [28]. The CEQ will be administered after the first treatment.

### Sample size

Eighty participants (i.e. 40 per group) with plantar heel pain (who satisfy the inclusion and exclusion criteria) will be recruited. An initial prospective sample size calculation estimated that 76 participants will provide 80% power to detect a minimally important difference of 13 points in the pain domain of the FHSQ [49] with a standard deviation of 20 points and an alpha set at 0.05. This sample size will also be sufficient to detect a minimally important difference of 19 mm for the other primary outcome measure, 'first-step' pain measured on a visual analogue scale.

### Statistical Analysis

Statistical analysis will be performed using the SPSS (SPSS Corp, Chicago III, USA) software. If the participant has bilateral symptoms, data from the most painful side will be recorded and analysed [50]. Data analysis will follow the intention-to-treat principle using all randomised participants [51] and missing data will be handled using a modified group mean substitution method [52]. This method involves substituting the missing data value with the mean baseline score plus the difference between the mean baseline and mean follow-up score for that particular group. Standard tests to assess continuous data for normal distribution will be used and transformation carried out if required.

Demographic and anthropometric characteristics (gender, age, mass, height, body mass index, waist to hip circumference ratio, sporting activities, foot posture using the FPI and the number of MTrPs located in the soleus, abductor hallucis, flexor digitorum brevis and quadratus plantae) will be determined for each treatment group. Summary statistics will also be calculated for duration of symptoms and side affected (left, right or both).

Outcomes measured at 2, 4, 6 and 12 weeks will be analysed. A linear regression approach to ANCOVA will be used to assess for differences in continuous outcomes between the two groups [53]. Appropriate non-parametric statistical tests will be used for outcomes that are nominal and ordinal scaled. The p-value will be set at 0.05.

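### Filling missing outcomes with the arm's own mean understates the standard error and pushes the type I error above the stated 0.05

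*Protocol article*

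**What the plan says.** The Statistical Analysis section of the protocol article settles the matter in a few sentences.

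- Analysis set: "Data analysis will follow the intention-to-treat principle using all randomised participants".
- Missing values: "missing data will be handled using a modified group mean substitution method".
- Formula: "This method involves substituting the missing data value with the mean baseline score plus the difference between the mean baseline and mean follow-up score", computed within the participant's own arm.
- Visits: "Outcomes measured at 2, 4, 6 and 12 weeks will be analysed".
- Model: "A linear regression approach to ANCOVA will be used to assess for differences in continuous outcomes between the two groups".
- Significance level: "The p-value will be set at 0.05".

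The Sample size section gives the numbers to be randomised: "Eighty participants (i.e. 40 per group) with plantar heel pain". The Outcome measures section makes week 6 the primary time point. The article mentions no multiple imputation, likelihood-based model, variance correction or sensitivity analysis for missing data, and gives no expected missing rate.

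**The concern.** The rule is a single, deterministic imputation that the later analysis treats as real data. This has three consequences.

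1. **False precision.** The filled values lie exactly on the arm mean, so they add nothing to the residual sum of squares, yet they enlarge n and the degrees of freedom. Confidence intervals become too narrow and p-values too small wherever outcomes are missing.
2. **A weaker covariate adjustment.** Filled outcomes do not vary with the participant's baseline score. They flatten the fitted baseline slope and waste some of the gain from ANCOVA.
3. **A strong assumption about dropouts.** The rule supposes that people who leave did as well, on average, as those who stayed in their own arm. It ignores their week-2 and week-4 scores. If leaving depends on pain, the treatment difference can be biased, in a direction set by who leaves.

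The label of intention to treat does not help. Everyone is counted, but the information is that of the completers. At stake is error control on both primary outcomes at week 6. The distortion of the test runs towards false positives, which is the error a sham-controlled efficacy trial most needs to avoid.

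**Working it through.** **Inputs from the protocol article.** 40 per arm, SD 20, difference 13 points, 80% power, alpha 0.05 (Sample size); ANCOVA on everyone randomised, tested at 0.05 (Statistical Analysis).

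**Assumptions.** Two-sided test; the same proportion missing in each arm, completely at random; 5% to 30% missing; baseline to follow-up correlation from 0 to 0.7.

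**Step 1: the plan's own sample size.** n per arm = 2(1.960 + 0.842)² × 20² / 13² = 37.2, rounded up to 38, so 76 in total. This matches the article. A one-sided test would give 60, so the design is two-sided.

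**Step 2: what is imputed.** With B the arm's mean baseline and F its mean follow-up, the filled value is B + (F − B) = F: one constant per arm and visit.

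**Step 3: effect on the standard error.** Let o of 40 be observed in each arm, with true within-arm variance σ².

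- The filled values add nothing to the sum of squares, so the pooled variance estimate averages σ²(o − 1)/39.
- The reported variance of the difference is that quantity × 2/40. The true variance is σ² × 2/o.
- Reported SE / true SE = √[((o − 1)/39) × (o/40)], or roughly o/40.

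Example, o = 32 (20% missing): √[(31/39) × (32/40)] = √0.636 = 0.797.

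**Step 4: effect on the type I error.** The test rejects when a true t statistic on 2o − 2 degrees of freedom exceeds the critical value on 78 degrees of freedom (1.991) multiplied by that ratio. For o = 32 the effective cut-off is 1.991 × 0.797 = 1.59, and the two-sided tail probability on 62 degrees of freedom is 0.118.

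**Step 5: check with the planned ANCOVA.** The null case was simulated with 40,000 replicates per cell, across correlations 0, 0.3, 0.5 and 0.7.

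| Missing per arm | Reported SE / true SE (exact, unadjusted) | Type I error (exact, unadjusted) | Type I error (ANCOVA, simulated) |
|---|---|---|---|
| 2 (5%) | 0.949 | 6.3% | 6.1–6.4% |
| 4 (10%) | 0.899 | 7.8% | 7.7–7.9% |
| 6 (15%) | 0.848 | 9.6% | 9.7–9.8% |
| 8 (20%) | 0.797 | 11.8% | 11.4–12.0% |
| 12 (30%) | 0.696 | 17.2% | 17.2–17.7% |

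The same ANCOVA on observed outcomes only gave 4.8–5.3% throughout, with a reported-to-true SE ratio of 0.99 to 1.00.

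At 20% missing and correlation 0.5, substitution reported a mean SE of 3.58 while the estimate actually varied with SD 4.52. Observed-only analysis reported 4.35 against 4.36. Substitution therefore claims more precision and delivers slightly less, as the flattened slope would predict. In the same setting with a true 13-point effect, power appears to be 90% under substitution and 84% on observed data. The apparent gain comes with a type I error of 11.8% in place of 5.0%.

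**Step 6: other readings of the sentence.** Type I error under correlations 0 to 0.7:

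- participant's own baseline plus the arm's mean change: 6.0–6.2% at 5% missing, 11.7–12.1% at 20%;
- mean of all baselines in the arm plus the completers' mean change: 5.9–6.3% at 5%, 10.8–11.9% at 20%.

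**The case against.** The best counter-argument concerns size. The harm scales with missingness, and the article states no rate. The only hint is the step from 76 calculated to 80 recruited, about 5%, where the true error is only about 6%. With one person missing per arm (2.5%) it is about 5.6%, and with none missing it is nil. The larger figures need an assumed 15% to 20% missing at a six-week end-point. This stands: the size is conditional and must be given as a range.

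Second, the method is described as modified and rests on a cited source that is not at hand, so the intended value might be the participant's own baseline plus the arm's mean change. In that case the filled values would not be constant and the flattened-slope argument would fall. This stands as a caveat on the mechanism, but Step 6 shows that the inflation is much the same.

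Third, informative dropout is plausible rather than documented. Table 1 stops treatment when symptoms resolve, but nothing says that assessments stop. The Participants section asks people to forgo physical therapy and most analgesics, which could lead non-responders to leave, but that is inference. Observed-data ANCOVA can also be biased when dropout depends on earlier pain, so bias is not peculiar to substitution. For these reasons no bias figure is relied on here. The standard-error defect needs no informative dropout.

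Finally, an unseen analysis plan does not excuse the point. The article does not leave missing data open; it names a method and gives its formula.

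**Conclusion.** The concern holds. The rule as written gives standard errors that are too small whenever outcomes are missing, for every continuous outcome analysed this way, including the primary week-6 comparison. With 40 per arm and data missing completely at random, a nominal 5% test has a true type I error of about 6% at 5% missing, 8% at 10%, 10% at 15% and 12% at 20%. The missing rates are assumptions. The result hardly changes with the baseline correlation or with the reading of the imputation sentence. Bias from informative dropout would come on top, with size and direction unknown.

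This should be corrected before the trial is analysed. Even if the eventual harm is small, the rule is fixed before dropout is known, it governs the primary analysis, and its error inflates the false-positive rate.

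**What to change.** Replace the substitution rule in the Statistical Analysis section.

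- **Primary outcomes.** Fit one linear mixed model for repeated measures to all observed scores at weeks 2, 4, 6 and 12, with baseline score, arm, visit, arm-by-visit and baseline-by-visit terms and an unstructured covariance. Take the week-6 contrast between arms as primary.
- **Acceptable alternative.** Multiple imputation within arm, using baseline and earlier visits, then the planned ANCOVA combined by Rubin's rules.
- **Secondary outcomes.** These are measured after baseline only at weeks 6 and 12 (Table 2), so use the same model with two visits, or the same imputation approach.
- **Sensitivity.** Add an analysis in which missing values are allowed to be worse or better than predicted, separately by arm. Mean substitution, if kept at all, belongs only here.

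The article names SPSS without version or modules, so check that the installed version covers the chosen method.

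The cost is one paragraph of wording, with no extra participants or visits. Intervals will be somewhat wider when data are missing, which reflects the information actually collected. The Discussion places the start of recruitment in the future, so the change could be made before any outcome is seen.

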**Methods:**

Eighty community-dwelling men and woman aged over 18 years with plantar heel pain (who satisfy the inclusion and exclusion criteria) will be recruited. Eligible participants with plantar heel pain will be randomised to receive either one of two interventions, (i) real dry needling or (ii) sham dry needling. The protocol (including needling details and treatment regimen) was formulated by general consensus (using the Delphi research method) using 30 experts worldwide that commonly use dry needling for plantar heel pain. Primary outcome measures will be the pain subscale of the Foot Health Status Questionnaire and "first step" pain as measured on a visual analogue scale. The secondary outcome measures will be health related quality of life (assessed using the Short Form-36 questionnaire - Version Two) and depression, anxiety and stress (assessed using the Depression, Anxiety and Stress Scale - short version). Primary outcome measures will be performed at baseline, 2, 4, 6 and 12 weeks and secondary outcome measures will be performed at baseline, 6 and 12 weeks. Data will be analysed using the intention to treat principle.

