#### Outcome measures

All primary outcome measures will be performed at baseline then 2, 4, 6 and 12 weeks using a blinded assessor (Table 2). Secondary outcome measures will be performed at baseline, 6 and 12 weeks. The primary end-point for predicting the effectiveness of dry needling for plantar heel pain (using the primary outcome measures) will be 6 weeks. All measures will be done prior to any treatment consultation.

**Table 2 T2:** Timeline for primary and secondary outcome measurements

Outcomes						
		**Baseline**	**2 weeks**	**4 weeks**	**6 weeks**	**3 months**

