#### Primary outcome measures

##### 1. Foot Health Status Questionnaire (FHSQ) - pain

The primary outcome measure will be the pain subscale of the Foot Health Status Questionnaire (FHSQ). The FHSQ has been validated (content, criterion and construct validity) [36]. It has high test-retest reliability (intraclass correlation coefficient ranging from 0.74-0.92) and a high degree of internal consistency (Cronbach's α ranging from 0.85 to 0.88) [36]. It has been used in similar trials that have evaluated the effectiveness of different interventions for plantar heel pain [25,37].

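### Two primary outcomes at 6 weeks are each tested at an unadjusted 0.05, with no rule on whether one or both must be positive

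*Protocol article*

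**What the plan says.** The article treats the two pain measures as joint primaries in most places. The abstract (Methods) begins "Primary outcome measures will be the pain subscale of the Foot Health Status Questionnaire and" and goes on to first-step pain. Table 2 lists both under its primary heading. The Sample size section calls VAS the other primary: "This sample size will also be sufficient to detect a minimally important difference of 19 mm for the other primary outcome measure".

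One time point is singled out for both, in Outcome measures: "The primary end-point for predicting the effectiveness of dry needling for plantar heel pain (using the primary outcome measures) will be 6 weeks".

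The entry for FHSQ pain uses the singular: "The primary outcome measure will be the pain subscale of the Foot Health Status Questionnaire (FHSQ"). It stands under a plural heading, as item 1 of 2, and says nothing about how the two outcomes rank.

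The sample size rests on FHSQ pain: "76 participants will provide 80% power to detect a minimally important difference of 13 points in the pain domain of the FHSQ", "with a standard deviation of 20 points and an alpha set at 0.05". For VAS the section gives a 19 mm target and no standard deviation, power or alpha.

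The Statistical Analysis section plans ANCOVA by linear regression for continuous outcomes at 2, 4, 6 and 12 weeks and closes with "The p-value will be set at 0.05".

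**The concern.** The Discussion states one primary aim: whether needling reduces plantar heel pain more than sham. Two outcomes answer it at 6 weeks, each at the full 0.05, and nothing says how their results combine. There are two simple readings. Either one significant result is enough, and the error rate for the primary question exceeds the stated 5%; or both must be significant, and the chance of success is lower than the power quoted for FHSQ pain.

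A split result is realistic. The FHSQ subscale is a questionnaire score, while the VAS rates pain on getting out of bed in the morning. If one is positive and the other is not, the article gives no reading, and the choice would be made after the results are known.

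**Working it through.** **Inputs from the article.** FHSQ pain: difference 13 points, SD 20, alpha 0.05, power 80%, N = 76; recruitment target 80, 40 per group (Sample size). Two primary outcomes, one primary time point, 0.05 per test (abstract, Table 2, Outcome measures, Statistical Analysis).

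**Assumed, because the article does not give them.** The correlation r between the two test statistics, and the power for VAS.

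**1. Reproduce the stated sample size.** Per arm, n = 2 × (1.960 + 0.842)² × 20² / 13² = 37.2, rounded up to 38, so N = 76. This matches. A one-sided test would give N = 60, so the calculation spends the whole two-sided 0.05 on FHSQ pain and reserves none for VAS. Power by the noncentral t distribution is 79.9% at 38 per arm and 81.9% at 40 per arm.

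**2. Either outcome counts.** Family-wise error = P(|Z1| > 1.96 or |Z2| > 1.96) with both nulls true and (Z1, Z2) bivariate normal with correlation r. At r = 0 this is 1 − 0.95² = 0.0975.

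| r | Family-wise error | Both falsely significant (10% minus the second column) |
|---|---|---|
| 0 | 9.75% | 0.25% |
| 0.3 | 9.5% | 0.5% |
| 0.5 | 9.1% | 0.9% |
| 0.7 | 8.3% | 1.7% |
| 0.9 | 7.0% | 3.0% |

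These count rejections in either direction. False claims in favour of real needling alone run from 4.9% (r = 0) to 3.5% (r = 0.9), against 2.5% for a single test.

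**3. Both outcomes required.** The error is the last column when both nulls are true, and at most 5% when only one is true, so alpha holds. Joint power can never exceed the lower of the two single powers. If VAS power is also taken as 81.9%, it is 0.819² = 67% at r = 0, 71% at r = 0.5 and 74% at r = 0.7.

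The VAS assumption matters. At 40 per arm, power for 19 mm by the noncentral t distribution is 92% if the VAS SD is 25 mm, 80% if it is 30 mm and 67% if it is 35 mm. At r = 0.5 the joint power is then 78%, 70% and 60%. So 67% to 74% is an illustration and not a bound.

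**4. Splitting alpha equally.** At 0.025 each, n = 2 × (2.241 + 0.842)² × 400 / 169 = 45.0, so N = 90 for 80% power on FHSQ pain. With 40 per arm, FHSQ power falls from 81.9% to 73.2% (noncentral t).

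**5. Ordered test, FHSQ pain then VAS.** VAS is tested only after FHSQ pain is significant. If FHSQ pain has no true effect, any false claim must start with a false rejection there, which has probability 5%. If it has a true effect, only VAS can be falsely rejected, at no more than 5%. Family-wise error is therefore at most 5%, with N and FHSQ power unchanged.

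**The case against.** The strongest reply is that the article never says a win on either outcome makes the trial positive. A level of 0.05 is also compatible with an ordered test or a both-required rule, since each of these tests at 0.05. The article is condensed, and a success rule is often left to an analysis plan that is not shown. Part of this stands: an error of about 9% is conditional on the either-outcome reading and on an assumed correlation, and it is not an established property of the trial. The reply does not remove the point. The article itself fixes two primaries, one time point and one unadjusted level, and it sizes the trial with the whole alpha on one of them. A later plan that split alpha would undercut the power stated here.

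Three stronger readings are tempting and are not supported:

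- A reader might count all eight outcome-by-time tests (two outcomes, four visits) as primary and arrive at a much larger error. Outcome measures limits the primary comparison to 6 weeks, so the primary family is two tests.
- A reader might take 80% power as stated for each outcome. It is stated for FHSQ pain only; for VAS the sample is merely called sufficient.
- A reader might treat the singular wording for FHSQ pain as a declared hierarchy, or as a serious contradiction. Under a plural heading and as item 1 of 2, it is loose wording and sets no order.

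It is also fair to say that the planned ANCOVA would raise power if baseline predicts outcome. The power figures above ignore this, as they use the unadjusted comparison that reproduces the article's N.

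**Conclusion.** The point holds in conditional form. As written, the plan lets either of two outcomes answer the single primary aim at 0.05 and does not say what counts as success. Under the either-outcome reading the two-sided family-wise error is between 7.0% (r = 0.9) and 9.75% (r = 0), above the nominal 5% throughout that range. Under the both-required reading the error is controlled, but power to succeed falls below the 82% for FHSQ pain alone, by an amount the article does not allow one to calculate. Neither simple reading keeps both the stated alpha and the FHSQ power for the primary conclusion. The article does not support a flat statement that the trial has a 9% false-positive rate.

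**What to change.** Before recruitment, which the article places in February 2011, state the rule:

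1. Test FHSQ pain at 6 weeks first, at two-sided 0.05. It is the outcome the sample size is built on.
2. Test first-step VAS at 6 weeks at two-sided 0.05 only if FHSQ pain is significant.
3. Treat weeks 2, 4 and 12 as secondary for both outcomes, in line with the 6-week primary end-point already named, and report them with confidence intervals.
4. Align the wording in the abstract, Table 2, the FHSQ pain entry, Sample size and Statistical Analysis.

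The cost is a few sentences, with no added participants and no loss of power for FHSQ pain. The downside is that a positive VAS with a negative FHSQ pain result could not be claimed as primary success. If the investigators do not accept that, requiring both outcomes or splitting alpha would also close the gap. The first lowers the chance of success; the second needs about 90 participants for 80% power on FHSQ pain, or accepts about 73% with 80.
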